## Abstract

**Background:**

In Luxembourg, the extensive phenomenon of school dropout is a prime policy concern in the light of individual, social and economic consequences. Although the authorities report an overall decrease of the national dropout rate, the proportion of early school leavers who remain without any specific occupation is still alarming. Therefore, this study intends a shift of focus from system-inherent to individual factors, including mental health and family correlates, to provide a more comprehensive analysis of the dropout phenomenon.

**Methods/Design:**

The objectives of this study are to investigate the type and prevalence of psychiatric disorders among school dropouts and to compare the findings with those by a matched control group of regularly enrolled students. Furthermore, family variables and socioeconomic status will be analysed, as they are factors likely to interfere with both educational attainment and mental health. A trained psychologist will use structured interviews and self-report forms to investigate for mental health issues, information on schooling, socioeconomic situation and family life. Controls will be matched for gender, age, school type and educational grade.

**Discussion:**

As school dropouts face a serious risk of long term professional and social marginalization, there is an evident need for action. Identifying psychosocial risk and protective factors of school dropout will deliver solid insight on how to conceive public health strategies for young people who may need a more customized support to carry out their academic potential.

**Trial registration:**

ClinicalTrials.gov Identifier: NCT01354236

## Background

This research is part of an "Interreg IV-A" project aimed at analyzing and promoting mental health in the trans-border zone of Saarland (Germany), Lorraine (France), Wallonia (Belgium) and Luxembourg (PPSM "Prévention et Promotion de la Santé Mentale"[1]). The PPSM project consists of promoting mental health by developing knowledge on risk and resource factors, implementing campaigns to sensitise for overall well-being and establishing an international knowledge network of good practice in mental health. In Luxembourg, the evaluation and promotion of mental well-being will focus on adolescents and young adults who dropped out of school and who may be more at risk to have mental health issues.

Although school dropout is not a recent topic, yet it has never been as discussed than in today's knowledge based society. The eclecticism of definitions and studies concerning early school leaving well reflect the complexity of the subject. In this article, the terms "school dropout" and "early school leaving" will be used interchangeably.

Definitions account for national specificities such as the educational system policies and the duration of compulsory education. The Organisation for Economic Co-operation and Development (OECD) and EUROSTAT have developed indicators that allow to compare national dropout rates, however conclusions should consider limitations due to the national specificities. Both indicators define school dropout as the "termination of schooling below upper secondary qualification and the absence of any educational program or training". They slightly differ on the age span, which spreads from 18 to 24 years for EUROSTAT and only from 20 to 24 years for the OECD.

In Luxembourg, since 2003, the Ministry for Education ("Ministère de l'Eduction Nationale et de la Formation Professionnelle" MENFP) has been a third source providing information on secondary school dropout. In contrast to the OECD and EUROSTAT, the ministry records dropouts of all ages, reported by the national school institutions. For the scope of this research project, we will focus on the data released by the MENFP because it is based on actual figures.

Between 2003 and 2006, the national authorities had to face dropout rates of more than 15%. As a result, they introduced accompanying and preventive measures to reduce linguistic and cultural risk factors that may impede educational engagement and vocational decisions. Since then, the dropout rate has overall declined. According to the latest figures, the national dropout rate, for the academic year 2008/2009, was set at 9% [2] and hence conceded with the European benchmark of no more than 10%. However the proportion of early school leavers who remain without any specific occupation is still alarming.

When questioned on their rationale for leaving school, students reported 1) difficulties in vocational guidance, 2) academic failure or the anticipation of failure, 3) a lack of incentive to pursue any formal education, 4) the lack of an apprenticeship, 5) personal reasons, or 6) health issues [2]. In the light of these statements, dropout prevention needs to consider what may underlie the reported difficulties, by examining factors relating to the student. Insight into the correlates that can influence alienation from school, and thus dropout, will be provided by exploring individual factors such as mental health, family life and socioeconomic situation.

Adolescence can be an unsettling period of life, marked by physical, psychological and social changes. It is known that up to 50% of lifetime mental disorders have their onset during adolescence [3] and that prevalence rates of at least one DSM IV disorder range from 13.7% [4] to 22.2% [5]. Such disorders include substance use, disruptive behaviour disorders, anxiety and mood disorders.

Nevertheless, in Europe, the exploration of early school leaving in terms of mental health is yet to mature, and only a few recent studies can be referenced. In France, Huerre and Leroy [6] presented a holistic analysis of school dropout, Brandibas [7] considered truancy to be associated with different types of anxiety, whereas Legleye [8] reported an association between dropout and the progression to daily cannabis use. Jonsson [9] pointed out that Swedish adolescents suffering from depression were less likely than their non-depressed peers to have graduated from higher education.

In North American and Canadian research literature, several studies explored the impact of mental health factors on academic attainment. They covered a whole spectrum of psychiatric disorders, and concluded that school dropout is not necessarily associated with motivational or institutional factors, but with serious social and cognitive impairments aroused by mental illness. Meldrum [10] confirmed the above hypothesis by revealing that up to 15% of Canadian students interrupted their studies for reasons of mental health. A recent study of a US national sample confirmed that 12 out of 17 psychiatric disorders were associated with subsequent failure to complete secondary education by the age of 18 [11]. After controlling for potential confounders, the authors established that bipolar and conduct disorders were most consistently related to early school leaving. In fact, several studies concluded that there was a significant association between school dropout, Attention Deficit (Hyperactivity) Disorder/AD(H)D [12] and disruptive behaviour disorders, also known as externalizing disorders [13,14]. For Kessler [15], the association with externalizing disorders was significant for males only, whereas so-called internalizing disorders were the most important psychiatric determinants of school dropout for females. Internalizing disorders include anxiety (specific phobia, social phobia, generalized anxiety disorder, panic disorder with or without agoraphobia, obsessive compulsive disorder and posttraumatic stress disorder) and mood disorders (major depressive disorder, bipolar disorder, dysthymia). In 2008, Fletcher [16] confirmed these findings by detecting a significant negative correlation between depression and high school attainment for females only; whereas Jonsson [9] did not observe any difference in gender.

In addition to the disorder categories mentioned above, substance abuse and dependence have significantly correlated with school dropout [13,17,18]. In their literature review, Townsend et al. analyzed 46 studies on the correlation between substance use and school dropout, and concluded that alcohol, tobacco and cannabis use had an impact on educational attainment and vice versa [19].

Regarding the consensus for a multifactorial approach to psychiatric disorders, we consider it crucial to investigate for risk factors and protective factors derived from the individual and social domains as well as interactions among those factors. Socioeconomic status (SES) was reported to have an impact on both mental health [20] and educational attainment [21]. Indeed, among students with a low SES, 44% of school dropout could be attributed to psychiatric disorder, whereas the proportion increased to 61% for students with a high SES [22].

In the same way, family variables correlated with both mental health [23,24] and education [25,26]. In 1996, Bernstein and Borchardt analyzed different types of family composition in school refusal. They found out that communication and role behaviour seemed to be problematic in mother-only households [27]. According to Bernstein, difficulties in role behaviour may reflect symptoms of separation anxiety in children, who refuse to leave home because they worry about or care for a physically or emotionally vulnerable parent [23].

In the light of previous research, we hypothesize that school dropouts have significantly more mental health problems than their peers who go to school. They are also more likely to report a poor socioeconomic background, negative school experiences (repeating classes, disciplinary measures, absenteeism, problematic relations with authority and peers) and difficulties in family functioning (task fulfilment, role performance, communication, affective expression, connectedness, control behaviour, values and standards).

### Research questions

The first objective of this research is to assess the type and prevalence of psychiatric disorders among early school leavers in Luxembourg and to compare the findings with those by a control group matched for gender, age, school and educational grade. If there is an association between mental illness and school dropout in Luxembourg, is it significant for only one psychiatric disorder or more (comorbid disorders)?

As a second objective, we aim to identify specific protective and risk factors derived from the individual and family domains by including school experiences, sociodemographic background and family variables (task fulfilment, role performance, communication, affective expression, connectedness, control behaviour and values and standards) in the analysis. These thematic analyses will establish which experiences are specific to school dropouts with mental health problems, which are specific to school dropouts without mental health problems, and which to students enrolled in regular secondary education.

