**Figure 1 F1:**
[figure not shown]
**Stages of field research**. Figure 1 gives an overview of field research stages, beginning with the selection of eligible participants realised in collaboration with the ministry and "Action Locale pour Jeunes" (ALJ), their recruitment and finally the evaluation procedure, which consists of face-to-face interviews.

Figure 1: Stages of field research

The recruitment of school dropouts will be incident and realised in collaboration with a service operated by the ministry and called "Action Locale pour Jeunes" (ALJ). Every month, the ALJ receives a listing of all school dropouts who they contact in order to find out about their current occupation. If needed, they provide academic or vocational support.

As we expect a major denial of participation, all eligible dropouts listed in a monthly record will be systematically contacted.

A preliminary telephone contact provides information on the study (objectives, procedure, expected benefits) and asks for participation. If the student is interested in participating, an appointment for the interview is immediately set up and informed consent will be sent. It should be noted that information avoids deterrent terms such as "psychiatric" or "mental" and rather refers to "personal wellbeing". Meetings with cases will be organised in the regional offices of ALJ as we consider it an uncommitted, well accepted site.

The recruitment of controls will be subsequent to the participation of dropouts. There will be one control per dropout who participated in the study. Expecting a major denial of participation, we will ask the ministry to get a selection of 5 matched controls per case. Among these 5 controls, selection will be randomised.

The recruitment and evaluation procedures will be same than for cases (cf. Figure 1), but interviews will take place at school and outside of school hours.

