### Sample size calculation

Considering an overall lack of prevalence rates of mental disorders in Luxembourg, we refer to the European Study of the Epidemiology of Mental Disorders [4] to assume a prevalence rate of 13.7% for any psychiatric disorder in the age group 18-24 years. Previous studies have reported a significant association between psychiatric disorders and subsequent school dropout by identifying odds ratios ranging from 1.0 to 5.7 depending on the disorder category [11,13,14]. To demonstrate that young adults with a psychiatric diagnosis compared with young adults without any psychiatric diagnosis have an odds ratio (OR) of at least 2.0 for dropping out of school, with alpha error set at 0.05 and statistical power of 80%, 146 participants per group will be needed.

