### Statistical analysis

To evaluate the representativeness of the school dropouts included in the study, a comparative analysis will be conducted on age, gender, educational grade, grade repetition, nationality, household composition and employment status.

Results will be expressed as mean and standard deviation (SD) for quantitative measurements and as frequency tables for categorical findings. The association between two continuous variables will be assessed by the correlation coefficient. Matched groups means values will be compared by two-way analysis of variance (or paired Student t-test) while the symmetry test (or McNemar Test) will be used for paired proportions. To identify variables associated with school dropout, we will conduct a conditional logistic regression analysis for matched pairs' data with school dropout as the outcome and psychiatric disorders, socioeconomic background and family variables as predictors of interest. The approach used to model psychiatric disorders within cases and controls with risk factors and/or prognostic factors will consist in a stepwise descending regression modeling technique starting from the full model in which all potentially and clinically important variables are included. Statistical control factors will concern demographic variables and school experiences. Comparison of embedded models will be done with the likelihood ratio test. Results will be considered as statistically significant at the 5% critical level (p < 0.05). All calculations will be carried out using the SAS^® ^System (Version 9.2 for Windows) statistical package and SPSSInc PASW Statistics 18.

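### The second objective splits dropouts by mental health but leaves enrolled students undivided, so a factor tied to mental disorder in everyone can be mislabelled as specific to dropouts with mental health problems

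*Protocol article*

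**What the plan says.** Under Research questions, the second objective brings school experiences, sociodemographic background and family variables into the analysis. Its stated purpose is to find out "which experiences are specific to school dropouts with mental health problems, which are specific to school dropouts without mental health problems". The same sentence then names regular students as one further group, with no split by mental health. That makes three groups: dropouts with problems, dropouts without, and all enrolled students together.

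Controls are assessed for disorder as well. The text under Figure 1 says of them: "The recruitment and evaluation procedures will be same than for cases".

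Statistical analysis describes two relevant models. One is a conditional logistic regression for matched pairs "with school dropout as the outcome and psychiatric disorders, socioeconomic background and family variables as predictors of interest". The other is a descending stepwise model, introduced as "The approach used to model psychiatric disorders within cases and controls with risk factors and/or prognostic factors". No test is assigned to the three-group question, no rule says when an experience counts as specific, and neither a four-group comparison nor a disorder-by-factor term is mentioned. The Background says it is crucial to investigate "risk factors and protective factors derived from the individual and social domains as well as interactions among those factors".

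**The concern.** To say that an experience is specific to dropouts with mental health problems, one must show that it is not simply a feature of anyone with such problems. The group that can show this is enrolled students with a disorder. In the objective as worded, that group is merged into the controls, most of whom have no disorder at the planning prevalence. Dropouts with disorder are then set against two groups that are wholly or mostly free of disorder, and any general correlate of disorder will tend to stand out in them.

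Such factors are to be expected here, since the Background itself reports that family variables and socioeconomic status are related to mental health as well as to education. The Abstract wants the findings to inform support strategies for young people. A general correlate of disorder reported as a marker of one kind of dropout would misdirect that advice.

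**Working it through.** **Inputs from the article.** Sample size calculation: 146 per group, odds ratio 2.0, and the authors "assume a prevalence rate of 13.7% for any psychiatric disorder in the age group 18-24 years". Background: a higher prevalence of 22.2%, used here as a sensitivity value.

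**The plan's own figure.** Disorder prevalence in dropouts is 2 × 0.137 / (0.863 + 2 × 0.137) = 0.274 / 1.137 = 0.241. The usual two-proportion formula for 24.1% against 13.7%, with 80% power and alpha 0.05, gives 222 per group two-sided or 175 one-sided. The matched-pair formula gives 219 two-sided. So 146 does not follow from the stated inputs. That is a separate matter, and 146 is used below only as the planned size.

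**Expected cells at 146 per group.**
- Dropouts with disorder: 146 × 0.241 = 35; without: 146 × 0.759 = 111.
- Controls with disorder: 146 × 0.137 = 20; without: 146 × 0.863 = 126.

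**Illustration (factor rates assumed).** Take a factor present in 20% of people without disorder, with odds ratio 3 for disorder and no link to dropout given disorder. Its rate with disorder is 3 × 0.2 / (0.8 + 3 × 0.2) = 0.6 / 1.4 = 42.9%. The three groups then show:
- dropouts with disorder: 42.9%
- dropouts without disorder: 20.0%
- all controls: 0.137 × 42.9% + 0.863 × 20% = 23.1%

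The factor looks peculiar to the first group, yet its rate in controls with disorder is also 42.9%.

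**How often the false label arises.** Assumed rule: significantly higher in dropouts with disorder than in each of the other two groups, by unpaired two-proportion z tests at 5%. There were 40,000 runs per setting, with base rates of 20% to 30%.

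| Factor-disorder OR (assumed) | Control prevalence 13.7% | Control prevalence 22.2% |
|---|---|---|
| 1 (no link) | about 1% | about 1% |
| 2 | 24–28% | 24–30% |
| 3 | 60–65% | 63–70% |
| 4 | 82–86% | 85–90% |

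**The same factor under other analyses.**
- Dropouts with disorder against controls with disorder: flagged in about 5% of runs, the nominal rate.
- Conditional logistic regression for dropout, adjusted for disorder (4,000 runs): 4–5%.
- Disorder-by-factor term added to that model: 4–5%.
- Test of the factor-disorder link in controls alone: found in 29–31%, 59–61% and 79–82% of runs at odds ratios 2, 3 and 4.

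**Precision of the like-with-like comparison.** With 35 against 20, power is 17–21% for a true odds ratio of 2, 39–47% for 3 and 60–67% for 4.

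**Precision of the interaction (unmatched approximation, rates 50% and 20%).** The variance of the log ratio of odds ratios is the sum of 1/[n p(1−p)] over the four cells: 1/8.75 + 1/17.76 + 1/5 + 1/20.16 = 0.420, so the standard error is 0.65. For 80% power the ratio must be about exp(2.80 × 0.65) ≈ 6. At a ratio of 2, power is about 19%.

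**The case against.** The strongest reply is that the three-group wording is a statement of aims and not an analysis. The article gives no rule for 'specific', so the simulated rule is the reviewer's. The analysis it does describe enters disorder and family variables together as predictors of dropout, and that model seldom mistakes a disorder-only factor for a dropout correlate. The second model uses disorder status in controls as well, so a general correlate of disorder could surface there. Nothing limits either model to main effects, and an article may leave the list of interaction terms to the full protocol. The Background's remark on interactions concerns risk and protective factors in general and does not promise a disorder-by-factor term. The factor rates are assumed, the family questionnaire is a 40-item scale and not a yes/no factor, and mental health problems are not equated with a MINI diagnosis. Finally, an interaction test has so little power that making it the sole gate would leave the objective nearly unanswerable.

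Most of this stands, and it limits the claim. It does not remove it. Adjusting for disorder asks whether a factor is linked to dropout overall. The objective asks whether the link belongs to dropouts with or without problems, and the models as described do not answer that. The model of disorder may miss a general correlate, since detection in controls alone ranges from about 30% to 80%, and nothing ties its result to the specificity conclusion. The choice of groups is fixed by the objective itself and is not a detail deferred elsewhere.

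**Conclusion.** The objective's three-group contrast cannot separate a correlate of disorder in everyone from one specific to dropouts with disorder. Under the assumed rule, the false label occurs in about 24% to 90% of simulated studies over factor-disorder odds ratios of 2 to 4, base rates of 20% to 30% and control prevalences of 13.7% to 22.2%, against about 1% when factor and disorder are unrelated. These figures rest on a binary factor, unpaired tests and disorder as the splitting criterion. They show that the problem can be large and do not forecast the study's error rate.

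Three stronger readings are not supported. A reader might infer that such a factor will be declared specific, or that following the plan correctly must give a wrong answer. Without a stated rule, and with a disorder-adjusted dropout model in the plan, neither follows. A reader might infer that the regression is confined to main effects, but the article is silent on that. A reader might also see a contradiction with the Background's call to study interactions, but that sentence is too general to bear it. The matter concerns the second objective and should be corrected. It does not touch the first objective's comparison of disorder prevalence.

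**What to change.** - Classify controls by the same mental health criterion as dropouts, and state which measure defines it.
- Report all four dropout-by-disorder groups with confidence intervals.
- Compare dropouts with disorder against controls with disorder, and dropouts without against controls without. Splitting by disorder breaks many matched pairs, so either adjust these contrasts for the matching factors or take them from the conditional model below.
- Add a disorder-by-factor term to the conditional logistic model as supporting evidence, not as the only route to a conclusion.
- Word specificity conclusions as exploratory.

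No new data are needed, because controls already receive the same evaluation; the change is to wording and analysis. The price is precision: with about 20 controls with disorder expected and roughly 20% power for a true odds ratio of 2, few specificity claims will be supported, and the report should say so.
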